## Methods

### Study design and participants

The project will investigate the effects of training frontline managers in hospitals in the Central Denmark Region through a cluster randomized waitlist controlled trial. The project aims to include 200 managers who, after registration and informed consent for the research project, are randomly allocated to receive either leadership training commencing in the beginning of 2023 (intervention group), or leadership training commencing in the beginning of 2024 (waitlist control group). Recruitment began in May 2022 and ended during January 2023. The participating managers are randomized by hospital ward, but the vast majority of wards include only one participating manager. Because some managers are clustered in wards, the wards are stratified into three groups of wards with: 1. One participating manager in the ward, 2. two participating managers, and 3. three or four participating managers. In each strata, wards are randomly assigned to equal sized intervention and control groups. For each strata, we randomly number all wards and using the RAND function in Excel, each ward is assigned with a random number between 0 and 1. The lowest 50% of numbers are assigned to the intervention group and the other 50% are assigned to the control group. In addition, the intervention group is randomly assigned to five training groups. The randomization is conducted by a neutral research assistant. All managers and their employees will be invited to complete outcome questionnaires at baseline prior to training, as well as 6-months and 12-months post baseline. An overview is presented in the flowchart in Fig. 1. Managers will also receive a short questionnaire related to the process evaluation following completion of each training module to assess the learning experience (see further description of the process evaluation below).

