#### Statistical analyses

To evaluate the intervention effects, we will examine group differences in the measured outcome variables over time. The analyses will consider the clustering of observations of staff within the team of the manager, as well as correlation of the repeated measurements within each staff member. The effect of the intervention will be estimated by three quantities: The difference between groups in mean change from T0 (baseline) to T1 (6-months), T0 to T2 (12-months) and T1 to T2 in the intervention groups versus the control group. Analyses will be conducted as intention to treat and where relevant compared to per protocol analyses. In general, the estimation will be based on a mixed model with time, group and an interaction of group and time as fixed effects. For outcomes measured at manager levels, the mixed model will include a random level for training group, hospital ward and manager. For outcomes measured at the employee level, an additional random level for employee is included. Analyses at the employee level will be further adjusted for employee age, gender, occupation, and span of control of the manager. Possible bias due to missing data will be investigated with a set of sensitivity analyses. Regarding turnover among the managers during the follow-up period, the two groups will be compared by binomial regression corrected for occupation, age, gender. Models will be bootstrapped over ward. The data analyst will be blinded as to who is in the intervention or control group.

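### Wards are randomised within three strata, but no stated model includes the stratum and the manager-level mixed models name no covariates; the cost is a little precision, not validity

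*Protocol article*

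**What the plan says.** Under Study design and participants, the article states: "The participating managers are randomized by hospital ward, but the vast majority of wards include only one participating manager". It gives the reason for stratifying: "Because some managers are clustered in wards, the wards are stratified into three groups of wards with" one, two, or three to four participating managers. Allocation is then balanced: "In each strata, wards are randomly assigned to equal sized intervention and control groups".

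Under Statistical analyses, the effect is defined as the between-group difference in mean change over each pair of time points. The general model is a "mixed model with time, group and an interaction of group and time as fixed effects". The further terms by outcome type are:

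- Manager-level outcomes: "the mixed model will include a random level for training group, hospital ward and manager". No covariates are named.
- Employee-level outcomes: a further random level for employee, and "Analyses at the employee level will be further adjusted for employee age, gender, occupation, and span of control of the manager".
- Manager turnover: "the two groups will be compared by binomial regression corrected for occupation, age, gender".

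The section also says that models will be bootstrapped over ward, without mentioning stratum or arm.

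**The concern.** Two things do not line up. First, the allocation is restricted by stratum, but the stated analysis takes no account of that restriction. The random ward level handles correlation among managers in the same ward; it does not represent the blocking. If strata differ in mean change, that variation stays in the model's standard error although the design has already removed it from the estimate, so the standard error is somewhat too large.

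Second, adjustment is uneven. Age, gender and occupation are used for employee outcomes and for manager turnover, but not for the manager-level mixed models. Those models serve manager self-care, staff-care, stress, burnout and job satisfaction, which the article lists as primary. They also rest on the smaller sample, 80 managers followed up per group. Age and gender come from the questionnaires and job titles from HR data, so nothing new need be collected. Leaving the adjustment open also leaves room to choose between adjusted and unadjusted results after seeing them.

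**Working it through.** **1. Inputs, from Sample size.** Effect size d = 0.54, baseline correlation r = 0.5, group size 20, intra-group correlation 0.02, 80 managers followed up per group, alpha 0.05 (taken as two-sided), stated power 0.83.

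**2. Reproducing the plan's figure.** Design effect = 1 + (20 − 1) × 0.02 = 1.38, applied to both arms. Change-score variance factor = 2(1 − 0.5) = 1.

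SE = √(1.38 × 2/80) = √0.0345 = 0.1857

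Power = Φ(0.54/0.1857 − 1.96) = Φ(0.947) = 0.828

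This matches 0.83. The alternatives do not: a baseline-adjusted variance of 1 − r² gives 0.919, no design effect 0.927, a one-sided test 0.897, and the design effect in one arm only 0.879. The stated power is therefore consistent with an analysis of change and no covariates.

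**3. What adjustment could add.** The documents give no figure for how well stratum or covariates predict change. Let R² be the assumed share of *change-score* variance explained, so that SE is multiplied by √(1 − R²).

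| Assumed R² | SE ratio | Power |
|---|---|---|
| 0 | 1.000 | 0.828 |
| 0.01 | 0.995 | 0.832 |
| 0.02 | 0.990 | 0.836 |
| 0.05 | 0.975 | 0.847 |
| 0.10 | 0.949 | 0.865 |
| 0.15 | 0.922 | 0.884 |

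**4. How much the stratum alone could supply.** Stratum sizes are not given. Assume 120, 14 and 4 wards with one, two and three managers: 120 + 28 + 12 = 160 managers, in shares of 0.75, 0.175 and 0.075. Score the strata 0, 1, 2. The mean is 0.325 and the variance is 0.175 + 4 × 0.075 − 0.325² = 0.369, so the SD is 0.608. For the stratum to explain 5% of variance, mean change would have to differ by √0.05/0.608 = 0.37 SD per step. That is a large gradient beside a planned effect of 0.54.

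**5. Does ignoring the stratum distort the test?** Stratified ward randomisation was simulated with the layout in step 4, without within-ward correlation, using 6,000 runs per setting (Monte Carlo error on type I error is √(0.05 × 0.95/6000) = 0.003). The true effect for power was 0.54/√1.38 = 0.46.

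| Stratum R² | Type I error, ignored | Type I error, included | Power, ignored | Power, included |
|---|---|---|---|---|
| 0 | 0.056 | 0.056 | 0.832 | 0.833 |
| 0.02 | 0.051 | 0.053 | 0.826 | 0.831 |
| 0.05 | 0.048 | 0.053 | 0.821 | 0.835 |
| 0.10 | 0.038 | 0.047 | 0.838 | 0.861 |

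At R² = 0.10 the mean model-based SE with the stratum ignored was 0.158, against an actual spread of estimates of 0.149. It is too large, never too small.

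**6. Which term is needed.** A mixed model was fitted to one simulated data set with three complete waves, in which the stratum shifted level but not change. The group-by-time contrast at the last wave was:

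- no stratum: 0.3506 (SE 0.1575)
- stratum main effect: 0.3506 (SE 0.1575)
- stratum and stratum-by-time: 0.3506 (SE 0.1578)

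A main effect does nothing for the contrast. The interaction costs almost nothing when the stratum does not predict change, and it is the only route to a gain when it does. Age, gender and occupation measured at baseline are also constant over time, so the same reasoning applies to them.

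**7. Bootstrap.** If W wards are resampled without restriction and a small stratum has k wards per arm, the chance that a resample contains no ward from at least one of that stratum's arms is 2(1 − k/W)^W − (1 − 2k/W)^W. Assuming W = 150, this is 25% for k = 2, 9% for k = 3 and 3% for k = 4. It does no harm while the stratum is absent from the model, and matters once it is added.

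**The case against.** The strongest reply is that nothing here is invalid. The target is change over time, so stable differences in level between strata cancel, and ward, the unit of randomisation, is already a random level. Unadjusted analysis of a randomised trial is sound. The stated reason for stratifying is clustering of managers, not prognosis, and with most wards in one stratum the factor is nearly constant. No passage says that stratum, age, gender or occupation predicts change. The model is introduced as a general form in a condensed article, and a fuller covariate list may sit in an analysis plan that is not shown. Adding the stratum to a binomial turnover model could itself create sparse cells.

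Most of this stands, and it limits the size of the point. It does not remove it. The section is not silent on covariates: it states the fixed effects and lists adjustment variables for two families of models, and what it states does not follow the randomisation or treat manager outcomes consistently.

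A reader might infer that the omission makes the standard errors invalid or inflates false positives. The simulation shows neutral to mildly conservative behaviour, and 1:1 allocation within strata gives no route to bias. A reader might also infer that all manager-level analyses are unadjusted. They are not: turnover is corrected for occupation, age and gender.

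**Conclusion.** The point holds as a modest improvement in precision and consistency. The randomisation stratum is in none of the stated models, and the manager-level mixed models alone name no covariates. There is no bias and no type I inflation, and the stated power of 0.83 needs no correction on this ground. The possible gain runs from nothing to about 0.037 in power (0.865 − 0.828) at an assumed R² of 0.10, or 0.055 (0.884 − 0.828, from unrounded values) at 0.15.

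These gains rest on three assumptions: R² is a share of change variance, not of outcome variance at one time; the variables enter with time interactions; and the manager sample-size inputs are right. The documents support no particular R², and the stratum's own share is probably at the low end. No gain is calculated for employee outcomes, because the article gives no employee-level power calculation.

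**What to change.** - In the manager- and employee-level mixed models, add the three-level stratum and its interaction with time.
- In the manager-level mixed models, prespecify manager age, gender and occupation at baseline, each with a time interaction.
- In the manager turnover regression, add the stratum where cell counts allow, merging the two multi-manager strata if they are sparse.
- Once the stratum is in a model, resample wards within stratum and arm in the bootstrap.

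The cost is wording in the analysis plan, fixed before unblinding, and no new data. The downside is a few degrees of freedom and possibly sparse cells in the smallest stratum, which the merging rule is meant to contain.

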#### Sample size

We estimated the number of participants using a power calculation based on survey measures and an expected moderate effect size of 0.54 (consistent with previous studies). We have adjusted for an individual baseline correlation of 0.5 and a group size of 20 with an expected intra-group correlation of 0.02. Participation is voluntary throughout the project and we expect a dropout rate of up to 20%. Based on these assumptions, we anticipate being able to recruit 100 managers per group and successfully to follow up on 80 per group. This would result in a satisfactory power of 0.83 using an alpha value of 0.05.

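### As described, the mixed models do not capture training-group correlation that arises after baseline, and they capture team-level change only if the ward bootstrap covers them

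*Protocol article*

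**What the plan says.** All the modelling text is in the Statistical analyses section of the protocol article. The effect is defined as the between-group difference in mean change over three intervals: T0 to T1, T0 to T2 and T1 to T2. The fixed part has time, group and their interaction. The random part is given in two sentences: "For outcomes measured at manager levels, the mixed model will include a random level for training group, hospital ward and manager" and "For outcomes measured at the employee level, an additional random level for employee is included". Neither says whether a level is an intercept only or varies with time. The section also undertakes to allow for clustering of staff within a manager's team. After the sentence on the binomial regression for manager turnover comes "Models will be bootstrapped over ward", with no statement of which models are meant.

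Two other sections bear on the point. Under Study design and participants, wards are the unit of randomisation, most wards have one participating manager, and "the intervention group is randomly assigned to five training groups". The Sample size section allows for "a group size of 20 with an expected intra-group correlation of 0.02".

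**The concern.** A random intercept for a training group, ward, manager or employee takes the same value at every time point, so it subtracts out of any change from T0. What can still be correlated is the change itself. A team's employees live through the same events between surveys, and managers trained together share trainers and discussions. The programme theory relies on change spreading from manager to team.

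Training group is the clearest case. The groups are formed at random and do not act before training starts, so they have no effect at T0, and they do not exist in the control arm. An intercept constant over time is the wrong form for such an effect. If shared change is left out, intervals for the primary outcomes are too narrow and the false-positive rate exceeds the nominal 5%.

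**Working it through.** **1. The plan's own power figure.** Inputs from Sample size: effect size 0.54, baseline correlation 0.5, group size 20, intra-group correlation 0.02, 80 managers followed per group, alpha 0.05 (taken as two-sided).
- Variance of change: 2(1 − 0.5) = 1.
- Design effect: 1 + (20 − 1) × 0.02 = 1.38.
- Effective number per group: 80/1.38 = 57.97.
- Power: Φ(0.54 × √(57.97/2) − 1.96) = Φ(0.947) = 0.828, against the stated 0.83.

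The figure reproduces on the change scale. The calculation counts managers, and The intervention section gives training groups of up to 20, so 0.02 most naturally describes managers within a training group. The trial was sized for that correlation.

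**2. Do intercepts cancel?** The generalised least squares standard error of group-by-time was computed on a test layout.
- Complete data: 0.200, whether the training-group and ward intercept variances are 0, 0.02, 0.1 or 0.5.
- With 20% missing: 0.2134 to 0.2136 at T1 over the same range.
- With a cluster-by-time variance of 0.02 added (complete data): 0.219.

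The named levels, read as intercepts, leave the standard error essentially unchanged. A time-varying term does change it.

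**3. Employee level, manager or ward clustering.** About 25 employees per manager (5,000/200). The documents give no ICC of change for employee teams, so it is assumed over a range. With D = 1 + (25 − 1) × ICC, the type I error without the bootstrap is 2[1 − Φ(1.96/√D)].

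| Assumed ICC of change | D | Type I, formula | Type I, simulated without bootstrap | Type I, simulated with ward bootstrap |
|---|---|---|---|---|
| 0.005 | 1.12 | 0.064 | – | – |
| 0.01 | 1.24 | 0.078 | 0.078 | 0.056 |
| 0.02 | 1.48 | 0.107 | 0.102 | 0.052 |
| 0.05 | 2.20 | 0.186 | 0.195 | 0.054 |

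The simulation used 80 wards per arm, one manager per ward and 2,000 runs. With 15 responders per manager and ICC 0.02, D = 1.28 and the error is 0.083.

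**4. Manager level, training-group correlation 0.02, intervention arm only.**
- Five groups of 16 followed: the intervention-arm design effect is 1 + 15 × 0.02 = 1.30. Averaged with 1 for the control arm this is 1.15, and the type I error is 0.068.
- Groups of 20: (1.38 + 1)/2 = 1.19, giving 0.072.
- Simulated: 0.074 without and 0.075 with the ward bootstrap, against 0.057 and 0.058 when there is no training-group effect.

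**5. Employee level with ward-robust standard errors.** Assume a team ICC of change of 0.02 and a training-group share t of change variance.
- Captured variance of the difference: v = 2[0.02 + 0.98/m]/80.
- Missed variance: t/5.
- Type I error: 2[1 − Φ(1.96/√(1 + (t/5)/v))].

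| Responders m | v | t = 0.002 | t = 0.005 |
|---|---|---|---|
| 15 | 0.00213 | 0.072 | 0.106 |
| 25 | 0.00148 | 0.082 | 0.130 |

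Simulation at m = 25 gave 0.075 and 0.131 with the ward bootstrap, and 0.148 and 0.214 without it.

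**The case against.** The strongest reply is that the article never calls the random levels time-constant. An article may leave the covariance structure to an analysis plan that is not shown, and this one states an intention to respect clustering within teams. In addition, the bootstrap sentence uses the plural, closes the modelling description and resamples the unit of randomisation. If it covers the mixed models, it carries manager and ward correlation into the standard errors whatever the random terms are.

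Much of that stands. A reader might infer that the planned standard errors ignore clustering altogether. The documents do not support this, because the bootstrap may cover every model and step 3 then returns the error to about 5%. A reader might also quote 10.7% as the employee-level error at the plan's own ICC. That is not supported either, because the 0.02 belongs to groups of 20 in a calculation counted in managers. Applying it to employee teams is an assumption.

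The reply does not reach training group. The article names its model terms and puts time only in the fixed part, so random intercepts are the ordinary reading. A ward bootstrap treats wards that share a training group as independent. The employee-level shares of 0.2% and 0.5% are assumptions about an indirect effect, but the manager-level figure uses the correlation for which the plan itself allowed.

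**Conclusion.** The point holds conditionally for teams and wards, and on either reading of the bootstrap for training groups. It takes the random levels as intercepts.

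- **Teams and wards:** no material inflation if the bootstrap covers the mixed models. Otherwise the employee-level type I error is about 6% to 19% over the assumed range of the ICC of change, with 25 employees per manager.
- **Training groups, manager outcomes:** about 7% instead of 5%, at the plan's 0.02. With most wards holding one manager, this is the main clustering that matters at manager level.
- **Training groups, employee outcomes:** about 7–8% or 11–13% with ward-robust standard errors, for assumed shares of 0.2% or 0.5%, a team ICC of change of 0.02 and 15 to 25 responders per manager.

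The excess at manager level is modest and the larger figures depend on values that the documents do not give. This should be fixed before the unblinded analysis, but it is not a defect that invalidates the design.

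**What to change.** 1. For manager and ward clustering, either add a random manager-by-time or ward-by-time effect, or state that the ward bootstrap, resampled within arm and stratum, supplies the standard errors for all mixed models.
2. Replace the training-group intercept with an effect present only at T1 and T2 and only in the intervention arm. Let it differ between T1 and T2, or it cancels again from that contrast. Use small-sample degrees of freedom such as Satterthwaite or Kenward–Roger.
3. If bootstrap standard errors are kept, say how the training-group component enters them, since resampling wards does not supply it.

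The change is to wording and code, with no new data. The cost is somewhat wider intervals and a variance component estimated from only five groups, which will be imprecise.

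### The random levels named for employee outcomes do not cover shared change within a manager's team, and nothing ties the ward bootstrap to those models

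*Protocol article*

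**What the plan says.** All of the following is in the Statistical analyses section of the protocol article unless another section is named.

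- **Effect measures.** There are three: "The difference between groups in mean change from T0 (baseline) to T1 (6-months), T0 to T2 (12-months) and T1 to T2".
- **Fixed part.** Estimation generally uses "a mixed model with time, group and an interaction of group and time as fixed effects".
- **Random part.** For manager outcomes, "the mixed model will include a random level for training group, hospital ward and manager". Then: "For outcomes measured at the employee level, an additional random level for employee is included". The employee model therefore has training group, ward, manager and employee. No interaction of any of these with time is mentioned.
- **Stated intent.** "The analyses will consider the clustering of observations of staff within the team of the manager"; correlation of the repeated measurements is to be considered as well.
- **Bootstrap.** After the sentence on the binomial regression for manager turnover comes "Models will be bootstrapped over ward". The next sentence concerns blinding of the analyst.
- **Randomization** (Study design and participants). "The participating managers are randomized by hospital ward, but the vast majority of wards include only one participating manager".
- **Clustering in the power calculation** (Sample size). It uses "a group size of 20 with an expected intra-group correlation of 0.02". The group size matches the training groups of up to 20 managers described under The intervention. It does not describe a manager's team of employees.

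**The concern.** A random intercept for training group, ward, manager or employee is the same number at every visit. It lets teams and people differ in level, but it subtracts out of any change between two visits. The group-by-time contrasts then draw their standard error from employee-level residual noise alone, as if colleagues' changes were independent.

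The design makes shared change likely, also under the null hypothesis. Employees are reached only through their manager. The process evaluation lists staff shortage, ward turnover, resources and senior-management support as context, and these act on whole teams in both arms between visits. A structure that handles clustering of levels therefore need not deliver the stated intent for the quantities being estimated.

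At stake are the employee versions of the six registered primary outcomes: self-care, staff-care, stress, burnout, job satisfaction and sickness absence. If the standard errors are too small, a programme with no effect on employees would be declared effective more often than the nominal 5%.

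**Working it through.** **1. The plan's own figure.** Inputs from Sample size: 80 managers per group at follow-up, effect 0.54, baseline correlation 0.5, group size 20, intra-group correlation 0.02, alpha 0.05 (two-sided assumed).

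- Design effect: 1 + 19 × 0.02 = 1.38.
- Variance of change: 2(1 − 0.5) = 1.
- Standard error: √(2 × 1.38/80) = 0.186.
- Power: Φ(0.54/0.186 − 1.96) = 0.828, against 0.83 stated.

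The figure reproduces. A baseline-adjusted variance (1 − 0.5² = 0.75) would give 0.919 and does not match. The power calculation thus appears to inflate the variance of *change* for clustering, but at the training-group level and for managers.

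**2. The cancellation.** For employee i of manager j at visit t, write the outcome as fixed effects + training group + ward + manager + employee + c(j,t) + e(i,j,t). Here c is a team-by-visit deviation. For an employee seen at both visits, the change contains only the differences in c and in e. The named levels leave out c, so its variance is absorbed into a residual treated as independent between colleagues.

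In 12 simulated data sets with 80 managers, 12 employees each and a within-team correlation of change of 0.05, models with manager and employee intercepts were fitted:

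- mean model standard error of the group-by-time contrast: 0.064;
- standard error under independence: √(4/960) = 0.065;
- true standard error: √((4/960)(1 + 11 × 0.05)) = 0.080.

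**3. Size if standard errors are model-based.** With ρ the within-team correlation of change and m respondents per team, the design effect is DE = 1 + (m − 1)ρ, and the true two-sided error is 2[1 − Φ(1.96/√DE)].

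The target of 5,000 employees for 200 managers gives m = 25 before non-response. A loss of 20% gives m = 20. The value m = 15 is an assumption (60% response). ρ is an assumption throughout.

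| ρ | m = 15 | m = 20 | m = 25 |
|---|---|---|---|
| 0 | 0.050 | 0.050 | 0.050 |
| 0.01 | 0.066 | 0.072 | 0.078 |
| 0.02 | 0.083 | 0.095 | 0.107 |
| 0.05 | 0.133 | 0.161 | 0.186 |

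Example: ρ = 0.02 and m = 25 give DE = 1 + 24 × 0.02 = 1.48. The standard error is 1 − 1/√1.48 = 18% too small. The error reaches 0.10 at ρ = 0.0175 (m = 25), 0.022 (m = 20) or 0.030 (m = 15).

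**4. Size if the ward bootstrap applies.** Balanced three-visit data were simulated with one manager per ward, 160 or 200 teams and 15 or 25 respondents (2,500 runs per cell; Monte Carlo standard error near 0.05 about √(0.05 × 0.95/2500) = 0.004). For ρ from 0 to 0.05, intercept-only standard errors gave an error of 0.052 to 0.186, close to the table. Resampling wards gave 0.046 to 0.061 in every cell.

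**The case against.** The strongest objection is that the remedy may already be in the plan. The bootstrap sentence says models, in the plural, while the preceding sentence describes one regression, and the sentence after it is plainly general. Ward is the unit of randomization. With mostly one manager per ward, resampling wards does little for manager turnover and much for employee outcomes. If that reading is right, there is no inflation. This stands as a possibility, and the conclusion is conditional on it. It does not settle the matter, because no text links the bootstrap to the employee models.

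A second objection is that the article speaks of random levels without calling them intercepts, introduces the model as general, and may leave the covariance structure to a statistical analysis plan. That is fair as far as silence goes. But the article does list the random structure, and on its ordinary reading the list is inadequate for the contrasts defined just before it. The point therefore concerns what is stated, and goes beyond missing detail.

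A third objection is that the size is borrowed. The 0.02 belongs to training groups of managers, and the documents give neither an employee-team correlation nor a correlation of change. This stands in full: 0.02 serves here only as a reference value.

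A reader might infer that the false-positive rate is about double or more. The documents do not support that. It needs the bootstrap to be confined to turnover, and a correlation of change of 0.0175 or more even with all 25 employees per manager responding. With 15 respondents at 0.02 the error is 0.083.

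**Conclusion.** The point holds in conditional form. Taken as intercepts, the four named random levels drop out of all three change contrasts, and model-based standard errors carry no between-team variance in change.

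- **Bootstrap confined to manager turnover:** the type I error for employee outcomes is above 0.05 for any positive within-team correlation of change. It is about 0.07 to 0.19 for assumed correlations of 0.01 to 0.05 with 15 to 25 respondents per team, and 0.05 at a correlation of zero.
- **Bootstrap covering the employee-level mixed models:** the error is about 0.05 and the concern disappears.

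The calculations assume equal team sizes and employees observed at all visits. It would go too far to say that the plan's employee tests are invalid. What can be said is that their validity depends on how one ambiguous sentence is read, although they concern registered primary outcomes.

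**What to change.** Make one of two changes in Statistical analyses, before the analyst is unblinded:

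1. Add manager-by-time random effects to every employee-level mixed model, with time as visit, and ward-by-time random effects for wards with more than one participating manager.
2. Or state that the ward bootstrap, or ward-clustered standard errors with a small-sample correction, applies to all employee-level mixed models as well as to manager turnover.

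In either case, say that the three change contrasts take their standard errors and confidence intervals from that variance.

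The cost is one sentence and either one or two random terms or a resampling step. No new data are needed. Confidence intervals for employee outcomes become wider than under the intercept-only model by a factor √DE. At a correlation of change of 0.02 that is √1.28 = 1.13 (15 per team) to √1.48 = 1.22 (25 per team). At zero correlation there is essentially no widening.

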### The intervention

The leadership training consists of five full-day training modules over five months from the beginning of the training delivered to groups of up to 20 participants. There will be additional meetings in smaller practice groups between each module to solidify content learned in the training modules.

The training modules are facilitated by two experienced Human Resource Development (HRD) consultants, employed in Corporate HRD in the Central Denmark Region and with expertise in organizational psychology and leadership development within the region. Short video presentations of research-based knowledge will be provided during the modules by researchers with expert knowledge in subjects relevant for the training.

The training group meetings between the modules will focus on transferring the learning from each module into the managers' daily working context. The first of the meetings will be facilitated by an HRD consultant to support a meeting structure and the psychological safety in the group and the training. The next three meetings will be conducted by the group itself.

During the waiting period, the control group will have the opportunity to participate in a meeting with introductory information on the project and the psychosocial work environment.

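### As written, the claim of an analyst blinded to arm conflicts with the plan's own mixed models, which need a training-group code that only the intervention arm has

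*Protocol article*

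**What the plan says.** All of this comes from the protocol article.

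- **Blinding** (Statistical analyses): "The data analyst will be blinded as to who is in the intervention or control group". The section does not say how the blind is kept or when it ends.
- **Manager-level model** (Statistical analyses): "the mixed model will include a random level for training group, hospital ward and manager".
- **Employee-level model** (Statistical analyses): "For outcomes measured at the employee level, an additional random level for employee is included". This level is added to the others, so training group stays in the model.
- **Who has a training group** (Study design and participants): "In addition, the intervention group is randomly assigned to five training groups". The intervention section adds that training is "delivered to groups of up to 20 participants".
- **Controls during follow-up**: their training starts in early 2024. Until then, "the control group will have the opportunity to participate in a meeting with introductory information on the project and the psychosocial work environment". No training groups, placeholder groups or masked codes are described for them.
- **Analysis sets** (Statistical analyses): "Analyses will be conducted as intention to treat and where relevant compared to per protocol analyses".

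**The concern.** To fit the stated model, the analyst needs a training-group variable. If that variable exists in only one arm, holding it amounts to holding the allocation list, and the blind promised in the same section is lost once the file is opened.

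What is at stake is the credibility of the safeguard. A blinded analyst protects the choices made once outcome data are in hand: whether to depart from the general model form, when a per-protocol comparison is relevant, and which missing-data sensitivity analyses to run. The article leaves these open. A separate analysis plan may settle them, and their being open here is not a fault in itself. But if any are made with the training-group code in view, a report that repeats the blinding sentence would credit the trial with a protection it did not have.

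**Working it through.** The blinding claim has no figure of its own, so the main check sets the statements side by side.

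**Step 1. What the code looks like by arm.** About 100 intervention managers in five groups gives 100 / 5 = 20 per group, which agrees with the stated maximum of 20. The intervention arm therefore has five levels of about 20 managers each. No level is defined for the other 100 or so managers.

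**Step 2. Ways to code the controls.**

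| Coding of controls | Does the variable show the arm? |
|---|---|
| Missing | Yes: empty means control |
| One common 'none' level | Yes: one level of about 100 against five of about 20 |
| Each manager a separate level | Yes: single-manager levels against shared ones |
| Placeholder groups with neutral codes in both arms | Not from this variable, but the article describes none |

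Under the first three codings, labelling the arms A and B does not help, because the arm with five shared groups is the trained one.

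**Step 3. Reach.** Employees are linked to a manager, so the code passes to them. With 5,000 employees split evenly (an assumption), 5,000 / 2 = 2,500 are identified as intervention and the rest as control.

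**Step 4. Which analyses are affected.** The mixed models for manager and employee outcomes contain the term. The binomial regression of manager turnover does not, so it does not break the blind by itself.

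**Step 5. Does the power calculation imply groups in both arms?** Inputs from Sample size: effect 0.54, baseline correlation 0.5, group size 20, intra-group correlation 0.02, 80 followed up per arm, alpha 0.05 (taken as two-sided), stated power 0.83.

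- Design effect: 1 + (20 − 1) × 0.02 = 1.38.
- Change-score variance factor: 2 × (1 − 0.5) = 1.
- Power = Φ(0.54 × √(80 / (2 × D)) − 1.96), where D is the design effect averaged over the two arms.
- Clustering in both arms, D = 1.38: Φ(2.907 − 1.960) = 0.828, which reproduces 0.83.
- Clustering in the intervention arm only, D = (1.38 + 1) / 2 = 1.19: Φ(3.131 − 1.960) = 0.879, which does not.

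The stated power thus treats both arms as clustered. That is the conservative choice and a common simplification. It does not show that controls were given groups, and nothing in the blinding point changes the sample size or the power.

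**The case against.** The strongest reply is that the article does not say controls carry no group code in the analysis file. They are to be trained in 2024, so future or placeholder groups are conceivable, and the power calculation is compatible with groups in both arms. Masking of codes, custody of the key and the end of the blind are matters that an analysis plan or data-management plan usually settles.

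Part of this stands. The conflict is with the text as written, and a masked workflow could preserve a blind. The absence of operational detail is not the point. The point is that the article claims a property and specifies a model which, with groups formed as it describes, removes that property. Placeholder groups would also attach a clustering term to controls who share no training during follow-up.

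Several stronger readings are tempting but not supported:

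- **That the blinded analyst is the main safeguard left because participants know their arm.** Blinding the analyst does nothing about self-report by unblinded participants. The article has other protections: randomisation by a neutral assistant, intention to treat, a stated model, and register data on sickness absence and turnover.
- **That the analyst has wide discretion.** The contrasts, fixed effects, random levels, employee-level covariates and bootstrapping over ward are all stated.
- **That the process evaluation breaks the blind too.** Its analysis section makes no claim of blinding, and the module surveys, answered only by the intervention group, need not reach the effect analyst early. The same holds for a per-protocol comparison run after the main models.

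**Conclusion.** The point holds in a limited form. As written, the blinding statement is incompatible with the mixed models in the same section, because the training-group code they need is defined in one arm only. Where that code is supplied raw, disclosure is complete for managers and linked employees in both arms.

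This rests on two assumptions: that controls have no training-group codes during follow-up, which is how the article describes the design, and that the analyst who fits the models is the one said to be blinded.

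A reader might infer that the trial's results will be biased, or that no blind is possible in this design. The documents support neither. The size of any analytic bias cannot be computed from them, and a workable blind can be set up. The point deserves correction because the claim will be carried into the report and the remedy is cheap.

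**What to change.** Replace the blinding sentence with a procedure that can hold:

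1. The analyst writes and locks all intention-to-treat code, including the missing-data sensitivity analyses, on a file with dummy arm and training-group codes. The dummy codes come from re-randomising wards within the existing strata.
2. The neutral research assistant who carried out the randomisation then swaps in the true codes, and the locked script is run.
3. Attendance and other training-related variables are released to the analyst only after that run.
4. The text states that the per-protocol and process analyses are not blinded.

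The cost is a few sentences in the protocol or analysis plan and a few hours of work for a person already in the trial. The one downside is small: corrections to the code after the lock must be logged. If the procedure is not adopted, the claim of a blinded analyst should be withdrawn for the mixed-model analyses. It need not be withdrawn on this ground for the manager-turnover regression.
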